### WOMAC Index LK 3.1

WOMAC is developed and recommended for evaluation of treatment effect of TKA [26,32]. The WOMAC Index includes 3 subscales: pain (7 items), stiffness (2 items) and physical function (17 items). The Likert scale version of the index will be used with the following description for all items: none, mild, moderate, severe, or extreme - corresponding to an ordinal scale of 0–4. The score in each subscale is standardized to a score of 0 to 100 with higher scores indicating more pain, stiffness and functional limitations.

Patients with osteoarthritis in the knee were involved during the development of the item inventory of the index in order to assess clinical relevance [26]. In comparison with several other instruments used to evaluate the consequences of osteoarthritis and generic measurements of health-related quality of life [26,32,33] the WOMAC Index has shown adequate properties in regard to validity.

The original, as well as European WOMAC Index Likert scale versions, have been tested as a patient completed questionnaire on TKA-patients pre- and post-surgery, presenting acceptable reliability concerning values for internal consistency (Crohnbach´s alpha y for pain .78 - .93; stiffness .75 - .93 and physical function .92 - .98) [26,34-36], and a test-retest reliability assessed by the intra-class correlation (pain .78 - 95, stiffness .67 - .90 and physical function .71 - .92) [34-36]. The ceiling and floor effect post-surgery were under 15% 6 months post-surgery, except for a ceiling effect at 15.79 for stiffness [37].

The responsiveness has been documented in several studies, and the mean changes at follow-ups 3 and 6 months post TKA-surgery were significant (p < 0.001) for all subscales [26,32,35].

The mean score of the subscale physical function 6 month post-surgery is estimated to 32 based on scores presented in the literature [38], allowing an improvement of 12 points as hypothesized.

### SF-36

The SF-36 is a generic measure of health status [39]. It yields an eight-scale profile of scores related to physical and mental dimensions of health based on the subscales: physical function (PF), role physical (RP), bodily pain (BP), general health (GH), vitality (VT), social functioning (SF), role emotional (RE), and mental health (MH). The dimensions represent the most frequently measured concepts in widely used health surveys, and they are the most affected by disease and treatment [40]. The answers in each subscale are converted to a score from 0 to 100, with higher scores indicating better health status.

SF-36 is recommended as a supplement to a disease specific measure to provide a broader insight into patients´ quality of life and allow comparison across conditions after TKA [32].

SF-36v2 in the acute form with a recall period of one week will be used in this trial.

### General self-efficacy scale

The uni-dimensional General Self-Efficacy Scale is developed to assess a general sense of perceived self-efficacy to predict coping with daily challenges and adaption after experiences of stressful life events. The scale can be applied after surgery as a mediator for health-related outcomes to assess changes in quality of life [28]. The scale encompasses 10 items, and the response to each item is made on a 4-points scale ranging from 1 = *not at all true* to 4 = *exactly true,* yielding a total score between 10 and 40. Higher score indicates higher level of self-efficacy [41].

### Data collection

From the medical records the following data are collected: age, gender, marital status, body mass index, ASA-group (American Society of Anesthesiologist physical status classification), co-morbidities, length of stay, and the code for the surgical intervention.

Further, the following patient-reported data are collected: level of education, occupational status, home care and nursing care at home, and inhibited physical function not caused by the TKA.

Additional patient-reported data about participation in the rehabilitation program, readmissions, and unscheduled contact with healthcare professionals (general practitioner, readmission and emergency department, doctor on call, the orthopaedic ward or the orthopaedic outpatient clinic) are collected as control for confounders.

Additionally, qualitative and quantitative data from the telephone follow-up consultations are documented in regard to duration as well as identified health problems and provided counselling related to the predefined themes structuring the intervention.

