### Aim

The aim of this trial is to evaluate the effect of a structured nurse managed telephone follow-up in the early rehabilitation period, based on the patient´s individual situation related to physical as well as psychosocial problems following TKA.

We hypothesize that telephone follow-up as a supplement to conventional treatment will improve health status and self-efficacy and reduce the number of acute clinical outpatient consultations after TKA compared to conventional treatment.

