### Secondary outcomes

Secondary analysis will assess the effect of telephone follow-up in the intervention group compared to the control group by change in pain and stiffness scores in WOMAC LK 3.1 Index, change in health-related quality of life measured by the Medical Outcomes Study Short Form (SF-36) [27], change in the General Self-Efficacy Scale score [28], and the number of acute visits to the orthopaedic outpatient clinic.

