### Randomization and blinding

Patients are randomized 1:1 to the intervention group or the control group respectively. The randomization is performed centrally by a web-based randomization program and in blocks unknown to the investigator and other subjects involved in the study. The randomization is executed just before discharge of the patients from hospital.

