### Intervention

The participants allocated to the intervention group receive telephone follow-up 4 and 14 days post discharge in addition to conventional treatment. A uniform structure of the consultations is based on key subjects for nursing status defined by the VIPS-model (the Swedish acronym for the concepts Well-being, Integrity, Prevention and Safety). The VIPS-model is a process-oriented documentation model developed to generate structured general information about the patient’s condition, needs, desires, problems and resources relevant for nursing to provide adequate nursing interventions and evaluation of the outcomes [30,31]. The nursing status is based on predefined key subjects identified as relevant to assess the health status in the course of disease [31]. The telephone follow-up consultations are structured and contain the following key subjects: communication, cognition/development, breathing/circulation, nutrition, elimination, sleep, pain/perception, skin/tissue, sexuality/reproduction, activity and psychosocial /spirituality/culture. The themes are supplemented with specific issues relevant to health status after TKA in regard to treatment and observation of the wound and the operated limb, management of painkillers, and ability to exercise as recommended. However, the course of the consultations may vary due to the individual needs of the patients.

All interventions are conducted by the researcher responsible for this trial. The adherence of the protocol for the intervention is assessed by audiotaping consultations executed the first Wednesday in each month. Subsequently the records are checked by an external research assistant to ensure compliance with the protocol.

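### Rehabilitation participation, readmissions and unscheduled contacts arise after randomisation and can be changed by the calls, yet the protocol collects them to control for confounding

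*Protocol article*

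**What the plan says.** The Data collection section of the protocol article separates medical-record items, patient-reported background items and a third set: "Additional patient-reported data about participation in the rehabilitation program, readmissions, and unscheduled contact with healthcare professionals". After listing the types of contact, it gives the purpose of this third set: "doctor on call, the orthopaedic ward or the orthopaedic outpatient clinic) are collected as control for confounders".

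Four other sections bear on this:

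- Randomization and blinding: "The randomization is executed just before discharge of the patients from hospital".
- Intervention: "The participants allocated to the intervention group receive telephone follow-up 4 and 14 days post discharge in addition to conventional treatment". The topics of the calls include "management of painkillers, and ability to exercise as recommended".
- Secondary outcomes: the list ends with "and the number of acute visits to the orthopaedic outpatient clinic".
- Aim: the calls are hypothesised to "reduce the number of acute clinical outpatient consultations after TKA compared to conventional treatment".

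The Outcome analysis section promises an intention-to-treat analysis. The only regression it names is a logistic regression, justified by the repeated measures, and it lists no covariates.

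**The concern.** A confounder of a treatment comparison is a common cause of treatment and outcome. Allocation here is random, and the variables in question come into being only afterwards, so they cannot be causes of allocation. They are possible consequences of it.

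Adjusting for a consequence of treatment does harm in two ways. If the calls improve function partly by getting patients to exercise or by averting problems, adjustment takes that part out of the estimate. If an unmeasured factor such as slow recovery or a complication drives both contacts and function, adjustment compares patients who had the same contacts but differ in that factor between arms. This can create a difference where none exists. In either case the estimate is no longer the total effect of being randomised to the calls.

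The protocol is also at odds with itself over one event: an acute visit to the orthopaedic outpatient clinic is a hypothesised effect of treatment in one place and a nuisance variable to be controlled in another.

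**Working it through.** **1. Order of events.** Randomisation is just before discharge (Randomization and blinding). The calls come 4 and 14 days after discharge (Intervention). Community rehabilitation, readmission and unscheduled contact can occur only after discharge. All three therefore follow randomisation.

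**2. Can treatment change them?** For acute outpatient visits, the Aim says so directly. For rehabilitation, the calls deal with the ability to exercise, so an effect is plausible. For readmissions and other contacts, the calls deal with the wound, the operated limb and painkillers, so an effect is again plausible, though it is not a stated hypothesis.

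**3. Overlap with an outcome.** Only the orthopaedic outpatient clinic component matches a named secondary outcome. Readmissions, rehabilitation participation and contacts with other providers do not.

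**4. The planned comparison.** Inputs from Sample size: difference 12 points, SD 18, α = 5%, power 90%, equal groups. The two-sided level is taken from Outcome analysis.

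n per group = 2 × (1.960 + 1.282)² × 18² / 12² = 2 × 10.51 × 2.25 = 47.3, rounded up to 48. The stated 48 is reproduced.

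Power at 48 per group: the standard error is 18 × √(2/48) = 3.674; 12 / 3.674 = 3.266; Φ(3.266 − 1.960) = 90.4%.

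**5. Illustration of lost effect.** Assumption: a share s of the 12 points runs through the adjusted variables. The remaining effect is 12 × (1 − s). The SD is held at 18 and n at 48 per group, which is a simplification because adjustment would also change the residual variance.

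| Assumed share s | Effect left (points) | Power |
|---|---|---|
| 0 | 12.0 | 90.4% |
| 10% | 10.8 | 83.6% |
| 25% | 9.0 | 68.8% |
| 50% | 6.0 | 37.2% |

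**6. Illustration of a spurious effect.** Assumptions: no true effect on function; the calls lower contacts by a standard deviations; an unmeasured recovery factor has loading r on both contacts and the function score (SD 18). Within arms, the slope of function on contacts is 18r². The adjusted group coefficient is therefore 0 − 18r² × (−a) = 18r²a. Higher WOMAC scores are worse, so a positive value counts against the intervention.

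| a | r | Formula (points) | Simulated, adjusted (points) |
|---|---|---|---|
| 0.25 | 0.3 | 0.41 | 0.40 |
| 0.25 | 0.5 | 1.13 | 1.09 |
| 0.50 | 0.3 | 0.81 | 0.80 |
| 0.50 | 0.5 | 2.25 | 2.25 |

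The simulation used 1,000,000 patients. The unadjusted difference was within 0.02 points of zero in every case.

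The values of s, a and r are assumptions. None of them is in the protocol.

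**The case against.** The strongest reply is that no adjusted analysis is actually specified. The Outcome analysis section describes two-group comparisons, paired tests and a logistic regression without covariates. The phrase in Data collection could be read loosely, as checking whether care received elsewhere differed between arms. Covariate lists are also commonly left to a statistical analysis plan, which is not shown. This stands as a limit: a reader might infer that the protocol has committed itself to a biased primary analysis, and the documents do not support that. It does not remove the point. Data collection states an analytic purpose, it is the only place that gives any variable a confounder-control role, and nothing in Outcome analysis restricts it.

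A second reply is that the numbers are invented and the spurious differences are small against a 12-point target. The illustrations do rest on assumptions, and they show the mechanism rather than the expected size. The argument does not depend on them.

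A reader might also infer that the acute-visit outcome rests on patient recall, because such contacts appear only among the patient-reported items. The documents do not say where that outcome comes from. The patient-reported contacts are given a different purpose, and an article may leave the data source to the full protocol. That inference is not made here.

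**Conclusion.** The point holds in conditional form. Variables that arise after randomisation, and that the calls can change, are assigned to confounder control, and one component overlaps a secondary outcome. If that purpose is carried out, the estimate is no longer the intention-to-treat effect.

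Neither the size nor the direction of the net bias can be derived from the documents. Under the stated assumptions, the loss is 1.2 to 6.0 of the 12 planned points for mediated shares of 10% to 50%, and the spurious difference under no effect is about 0.4 to 2.3 points against the intervention. It would be too strong to say that all the listed variables are trial outcomes, because the overlap is confined to outpatient clinic contacts.

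**What to change.** 1. In Data collection, delete the confounder-control purpose for rehabilitation participation, readmissions and unscheduled contacts. Keep collecting the data.
2. State that any adjustment in the effect models is limited to variables fixed before randomisation, for example age, sex, body mass index and ASA group.
3. If the baseline score is used as a covariate, say openly that it is not a pre-randomisation measure. Outcome measures defines baseline as 3 days after discharge. That is after randomisation, in patients who are not blinded, and only one day before the first call is due on day 4.
4. Report these variables by arm as outcomes or process measures. If their role in the effect is of interest, examine it in a clearly labelled mediation analysis, separate from the intention-to-treat comparison.

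The cost is wording only. With these variables left out of the effect model, the planned comparison stays at 48 evaluable patients per group, 12 points and about 90% power.

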### Sample size

Calculation of the sample size is based on the primary outcome physical function in the WOMAC Index based on the smallest clinically relevant improvement, which is reported to 5.3, 11.8 and 20.4 points related to low, intermediate and high baseline score tertiles respectively [42]. A difference of a minimum of 12 points in favour of the intervention group compared to the control group during a period of 12 months post-surgery is assessed as a clinical relevant outcome in this trial and determined as basis for estimation of the sample size. The standard deviation for the entire population is estimated to 18 points. Sample size is calculated with the assumption of normally distributed data with α = 5% and 1-β = 90% and an equal number of patients in each group. It is estimated that 48 patients are needed in each group. With an expected drop out rate of 20% 58 patients have to be included in each group.

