**Method/design:**

The design is a randomized un-blinded parallel group clinical trial conducted at the Department of Orthopaedic Surgery, Gentofte Hospital, the Capital Region of Denmark. In total, 116 patients will be allocated by an external randomization program to 2 groups: an intervention group following usual treatment after discharge supplemented by a nurse managed structured follow-up consultation conducted by telephone 4 and 14 days after discharge from hospital and a control group following treatment as usual. The consultations are structured by key subjects relevant to assess the health status according to the VIPS-model (the Swedish acronym for the concepts Well-being, Integrity, Prevention and Safety). The content of the consultations can vary according to the patients´ individual situations and needs. All consultations are conducted by the researcher responsible for the trial.

The effect is measured 1, 3, 6 and 12 months post-surgery. The primary outcome is self-reported physical function measured by The Western Ontario and McMaster Universities Arthritis Index. Secondary outcomes are self-reported health-related quality of life, general self-efficacy and the number of acute visits to the orthopaedic outpatient clinic.

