### Outcome analysis

Data will be entered in EpiData version 3.1. The statistical software STATA will be used for data analysis. Ratio-scaled data from both groups (intervention and control) will be compared by using parametric methods if data are normally distributed, and if not, nonparametric methods will be used. Nominal scale data will be compared by Chi-square test or by a 95% confidence interval when comparative measures. Categorical variables will be compared using the Pearson´s chi-square test and the Mann–Whitney test, and two-sided level of significance p < 0.05, if it is found optimal. For continuous data changes within the groups will be analysed by using a paired t-test. P < 0.05 will be considered as being statistically significant. Due to the repeated measures a logistic regression analysis will be performed.

All patients will be analysed in the groups to which they are randomly allocated according to intention to treat analysis. This analysis is primarily based on imputation of outcomes by carrying the last known outcome status forward and is supplemented by sensitivity analysis to examine the effect on the results.

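### A 20% drop-out allowance on 48 per group gives 60, not 58; the slip is minor and leaves about 89% power among completers

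*Protocol article*

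**What the plan says.** The Sample size section of the protocol article bases the calculation on WOMAC physical function. The target is "A difference of a minimum of 12 points in favour of the intervention group compared to the control group". The variability is given as follows: "The standard deviation for the entire population is estimated to 18 points". The error rates and allocation are "α = 5% and 1-β = 90% and an equal number of patients in each group".

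From these inputs the section concludes: "It is estimated that 48 patients are needed in each group". The next sentence adds the allowance for losses: "With an expected drop out rate of 20% 58 patients have to be included in each group". The Method/design paragraph of the Abstract carries the doubled figure forward: "In total, 116 patients will be allocated by an external randomization program to 2 groups".

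The sample-size paragraph does not say whether the test is one- or two-sided. The Outcome analysis section refers to a two-sided 5% level. That section also plans an intention-to-treat analysis that relies primarily on carrying the last known outcome forward, with sensitivity analyses in addition.

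**The concern.** The requirement of 48 per group and the allowance for 20% loss stand in adjacent sentences, and 58 does not satisfy both. If 20% of 58 are lost, fewer than 48 remain. The usual cause is adding 20% to the required number instead of dividing it by the proportion retained, and 58 is what that mistake would give.

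At stake is the internal consistency of a core design figure, one that is likely to be repeated in the final report. As written, 90% power, 20% drop-out and 116 patients cannot all hold on the article's own reasoning, which treats 48 as the number needed after losses. The adequacy of the trial is not seriously in question.

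**Working it through.** **Inputs (protocol article).** Difference 12 points, SD 18, α 5%, power 90%, equal groups, 48 per group before losses, 20% drop-out and 58 per group (Sample size); 116 in total (Abstract, Method/design). Two-sided testing is taken from Outcome analysis.

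**1. Reproduce the base figure.** For two means with equal groups,

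n = 2 × (1.96 + 1.2816)² × (18/12)² = 47.28, rounded up to 48.

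This matches the article. A one-sided test would give 39, so the calculation was two-sided.

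**2. Apply the drop-out allowance.**

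- Dividing by the proportion retained: 48/(1 − 0.20) = 60 per group, 120 in total.
- Starting from the unrounded figure: 47.28/0.80 = 59.1, again 60 per group.
- Multiplying by 1.2: 48 × 1.2 = 57.6, rounded up to 58. This is the stated figure. That it was obtained this way is inferred from the match.

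The gap is 2 per group and 4 in total (4/116 = 3.4%).

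**3. What 58 per group provides.**

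- At 20% loss: 58 × 0.80 = 46.4 remain, below 48 and below the unrounded 47.28.
- Loss at which 48 remain: 1 − 48/58 = 17.2%.

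**4. Power among completers.** Normal approximation: power = Φ(12/(18 × √(2/n)) − 1.96). For n = 46 the ratio is 12/3.753 = 3.197, so power is Φ(1.237) = 89.2%. For the t-test, the noncentral t distribution is used with 2n − 2 degrees of freedom and the same ratio as noncentrality parameter.

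| Completers per group | Normal approximation | t-test |
|---|---|---|
| 48 | 90.4% | 89.8% |
| 46.4 | 89.5% | 88.8% |
| 46 | 89.2% | 88.6% |

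Compared on the same scale, going from 48 to 46 costs 90.4 − 89.2 = 1.2 points or 89.8 − 88.6 = 1.2 points. Against the nominal 90%, the shortfall runs from 0.5 points (46.4, normal) to 1.4 points (46, t-test). The t-test figure is slightly under 90% even at 48, so it should not be set against 90% as though the whole gap came from drop-out.

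**5. The planned analysis with outcomes carried forward.** If every randomised patient has a value to carry forward, 58 per group are analysed. Power then depends on how much of the effect the carried values hold. As an illustration, assume 20% lost in each group, SD still 18, and the normal approximation:

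- Carried values hold the full effect: difference 12, standard error 18 × √(2/58) = 3.343, power Φ(12/3.343 − 1.96) = about 95%.
- Carried values hold no effect: difference 0.8 × 12 = 9.6, power Φ(9.6/3.343 − 1.96) = about 82%.

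The second case is an extreme but has a basis in the schedule. Baseline is defined as 3 days after discharge (Outcome measures) and the first call comes on day 4 (Intervention), so a patient lost before the 1-month questionnaire would carry forward a score from before the intervention.

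**The case against.** The strongest objection is that the shortfall is too small to matter. By the approximation that reproduces 48, the 46.4 expected completers give 89.5%, and they fall short of the unrounded requirement by 47.28 − 46.4 = 0.88 patients per group. The SD of 18 is itself an estimate: at 17.8, 46.4 per group would already give 90%. This stands, and it is why the point is minor. It does not make the sentence correct, because 48, 20% and 58 still disagree.

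The second objection is that completers are not the analysed sample. Outcome analysis and the Discussion both commit to analysing everyone as randomised, and the first questionnaire is handed over before discharge, so most patients who drop out may have a score to carry forward. This also stands, and it limits the claim. A reader might infer from the slip that the trial fails to deliver 90% power. The document does not support that for the planned primary analysis, whose power could lie above or below 90% depending on when patients are lost. The same uncertainty means that carrying outcomes forward cannot be cited as restoring 90%. The inflation to 58 also has a purpose only if 48 is read as the number needed after losses, so judging the sentence on completers is judging it on its own terms.

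Finally, the multiplication by 1.2 is not shown in the article. That is correct, but the inconsistency does not depend on how 58 was reached.

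**Conclusion.** The stated allowance is wrong as written. For 48 evaluable patients per group at 20% drop-out, 60 per group (120 in total) are needed, not 58 (116). With 58, about 46 per group complete and power among completers is about 89%, roughly 1.2 points below its value at 48 on either scale. This rests on the article's own inputs (12 points, SD 18, two-sided 5%), on 20% loss in each group, and on a comparison of completers.

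The shortfall is minor and has no material effect on the design. A conclusion that the trial is underpowered, or that it needs more patients, would go beyond what these figures show.

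**What to change.** Keep 116 patients and replace the drop-out sentence in the Sample size section with wording such as:

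*58 per group retains 48 completers (about 90% power, normal approximation) up to about 17% drop-out; at 20% drop-out about 46 per group complete and power among completers is about 89%.*

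The total of 116 in the Abstract can then stay as it is. The cost is one sentence, with no extra patients and no change to the design or analysis. The Results section reports half of the intended participants enrolled, so the restatement does not interfere with recruitment.
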